## Abstract

**Background:**

Dengue is a mosquito-borne disease caused by four distinct, closely related dengue viruses (DENV). Global dengue incidence has markedly increased in the past decades. The World Health Organization reported that cases increased from 505,430 in 2000 to 5.2 million in 2019. Similarly, the total dengue cases in Malaysia increased from 7,103 in 2000 to a peak of 130,101 in 2019. Knowledge, attitude, and practice (KAP) remain the most effective dengue prevention and control tools. Furthermore, school-based health education is key to enhancing knowledge and raising awareness of the seriousness of dengue among schoolchildren and transferring knowledge and practice from classrooms to homes. Thus, it is necessary to plan an integrated module for the primary prevention of dengue infection, specifically among schoolchildren.

**Aims:**

The present study intends to develop, implement, and evaluate the effectiveness of a theory-based integrated dengue education and learning (iDEAL) module in improving the KAP, environmental cleanliness index, and dengue index among schoolchildren in Selangor and Kuala Lumpur.

**Methods:**

This study is a single-blinded, cluster randomised controlled trial to be conducted from 1 September 2023 to 31 August 2025. The study will involve 20 primary and 20 secondary schools in Selangor and Kuala Lumpur. The 1600 participants will be randomly allocated to intervention and control groups based on selected clusters to avoid contamination. A cluster is a comparable school that fulfils the inclusion and exclusion criteria. The intervention group will receive the iDEAL module, while the control group will receive standard education. The iDEAL module will be developed following a systematic procedure and delivered in-person by trained researchers to the participants. The outcome will be measured using validated, self-administered questionnaires at baseline (T_0_), immediately (T_1_), one month (T_2_), and three months (T_3_) post-intervention to measure the intervention module effectiveness. The data will be analysed using IBM Statistical Package for Social Science (SPSS) version 28 and descriptive and inferential statistics. Within-group changes over time will be compared using one-way repeated measure analysis of variance for continuous and normally distributed variables. Within-group analysis of categorical data will use Cochran’s Q test. The main effect and interaction between and within the intervention and control groups at T_0_, T_1_, T_2_, and T_3_ will be tested using the generalised linear mixed model (GLMM). Hypothetically, the KAP, environmental cleanliness index, and dengue index among the intervention group will be significantly improved compared to the control group. The hypothesis will be tested using a significance level with a p-value of 0.05 and a confidence interval of 95%.

**Conclusions:**

The study protocol outlines developing and testing an iDEAL module for schoolchildren in Selangor and Kuala Lumpur, with no socio-demographic differences expected. The intervention aims to improve KAP, environmental cleanliness index, and dengue index, potentially reducing dengue risk. Results could inform public health policies, emphasizing school-based interventions’ importance in combating diseases like dengue.

## Introduction

Dengue is a disease caused by four distinct, closely related dengue viruses (DENV) and transmitted to humans through infected mosquito bites [1]. Dengue imposes a substantial burden on many tropical and sub-tropical regions [2]. Furthermore, the recent global dengue incidence has increased markedly. The World Health Organization (WHO) reported that cases increased from 505,430 in 2000 to 5.2 million in 2019 [1]. Moreover, the total dengue cases in Malaysia increased from 7,103 in 2000 to a peak of 130,101 in 2019 [3, 4]. As the previous peak was in 2019 and based on a cyclical pattern that peaks every four to five years, dengue is expected to peak in Malaysia in 2024 [3]. Selangor and Kuala Lumpur recorded the highest number and incidence of dengue cases and deaths in Malaysia.

The dengue clinical manifestations vary from mild illness to severe complications, where people who contract a secondary infection caused by a different DENV serotype have a higher risk of severe disease [5]. The initial dengue symptoms resemble those of other febrile illnesses and frequently result in misdiagnosis and incidence underestimation [6, 7].

The economic and resource burden on health services remains substantial in dengue-endemic settings [8]. Global estimates stated that there were 58.4 million symptomatic dengue virus infections in 2013, which included 13,586 fatal cases, and dengue illness reflected a total annual global cost of $8.9 billion [9]. Similarly, dengue infection imposes a significant economic burden in Malaysia. A 2013 study reported that the economic burden of dengue illness was $102.25 million annually and approximately $3.72 per capita [10]. The overall economic burden of dengue would have been even higher had the study included the costs associated with dengue prevention and control, dengue surveillance, and long-term dengue sequelae [10].

Accordingly, knowledge, attitude, and practice (KAP) remain the most effective tools against dengue infection [11–14]. School-based health education is key to enhancing knowledge, raising the awareness of the seriousness of dengue among schoolchildren, and transferring knowledge and practices from classrooms to homes [15]. Thus, it is necessary to plan an integrated module for the primary prevention of dengue infection among schoolchildren.

The authors intend to develop, implement, and evaluate the effectiveness of a theory-based integrated dengue education and learning (iDEAL) module in improving the KAP, environmental cleanliness index, and dengue index among schoolchildren in Selangor and Kuala Lumpur. The specific objectives are to develop the iDEAL module, determine and compare the baseline sociodemographic, socioeconomic, and dengue infection history between intervention and control groups, and evaluate the within- and between-group effects of the iDEAL module in improving the KAP, environmental index, and dengue index at baseline (T_0_), immediately (T_1_), one month (T_2_), and three months (T_3_) post-intervention.

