### Study duration

The study will be conducted over 24 months, from 1st September 2023 to 31st August 2025. Data will be collected from 1st November 2023. The study will comprise research planning, iDEAL module development, implementation, and evaluation of the intervention effectiveness. Fig 1 depicts the enrolment, intervention, and measurement schedule and corresponding assessment times.

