### Blinding

This study will use single-blinding, where the participants will not be aware of their group status. Single-blinding aims to minimise performance bias (the Hawthorne effect), where the participant might alter their responses or behaviour if they are aware of their allocated group. It is not be possible to blind the field researcher, who will deliver the intervention module to the participants. Participant single-blinding is possible in this study, as the participants will not know whether they are receiving the intervention module or standard care. The intervention module is defined as the iDEAL module in addition to standard care, while standard care is defined as the current programme conducted by schoolteachers, district health offices, or local authorities. The intervention and control groups will receive standard care, as it is part of the dengue prevention and control programme established by the local health authorities.

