## Data collection

Upon initiating the study, the liaison officer will obtain consent from the students who fulfil the eligibility criteria. Subsequently, T_0_ data will be obtained from the students who consent to participate in the study. The participants allocated to the intervention group will be given appointments within one month for intervention package delivery according to class. The total duration of the intervention sessions will be approximately 30 minutes in three meetings. After completing the intervention, the participants will be required to answer the post-intervention assessment measuring the study outcome at T_1_, T_2_, and T_3_. The control group will undergo the same assessment as the intervention group at T_0_, T_1_, T_2_, and T_3_. Fig 3 depicts the study flow diagram based on the CONSORT 2010 statement [20].

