## Data analysis

The data analysis will involve the intention-to-treat analysis strategy. The approach analyses the results in a randomised study, where all randomised participants are included in the statistical analysis and analysed according to the group they were originally assigned, regardless of the treatment received.

The collected data will be analysed using IBM SPSS version 28 and descriptive and inferential statistics. Data exploration will be performed to identify data entry errors, missing data, and outliers. Subsequently, the numerical data will be identified as normally or non-normally distributed via statistical and graphical methods. The statistical method will involve calculating the skewness or standard error (SE) of skewness and the Kolmogorov-Smirnov parameter, while the graphical method will involve plotting and analysing histograms and stem and leaf box plots. Normally distributed data will be described using mean and standard deviation, while non-normally distributed data will be described using median and the first and third quartiles (Q1, Q3). Categorical data will be presented as frequency and percentage.

The hypothesis will be tested using a significance level with a p-value of 0.05 and a confidence interval of 95%. Results that yield a p-value < 0.05 will be considered statistically significant. For between-group comparisons, the mean difference of continuous and normally distributed data between the intervention and control groups will be compared using the independent sample *t*-test. For continuous but non-normally distributed data, the intervention and control groups will be compared using the Mann-Whitney U test. The frequency difference of categorical data between the intervention and control groups will be compared using the chi-square test. Fisher’s exact test will be used for data from 2 × 2 tables, which contain >20% cells with an expected count < 5.

Within-group changes over time will be compared using one-way repeated measure analysis of variance (ANOVA) for continuous and normally distributed variables. Cochran’s Q test will be used for within-group analysis of categorical data. The main effect and interaction between and within the intervention and control groups at T_0_, T_1_, T_2_, and T_3_ will be tested using the generalised linear mixed model (GLMM).

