## Strengths and limitations

This study will involve a systematic intervention module development that includes a literature review, need assessment for the relevant target population, and SME. This approach influences the intended outcome and ensures an effective end product. The risk of contamination will be minimised via cluster randomisation. Ensuring that the selected schools are 10 km away from each other would further minimise the contamination risk. Thus, the intervention module effect on the intended outcome can be precisely measured.

Although the module development, implementation, and effectiveness assessment measures in this study are robust, the intended KAP outcome measurements will be self-reported. A self-administered questionnaire remains an appropriate measurement in a community intervention study focusing on the individual influence on KAP. Additionally, the researcher will measure the environmental cleanliness index and dengue index, which will provide reliable and valid measurements.

One possible challenge in this study is limited enrolment. In this instance, the researchers will adjust the recruitment methods, extend the enrolment periods, and cooperate with other research institutions. Education, regular contact, reminders, support services, and incentives increase participant adherence. Pre-defined assessment, reporting, and intervention protocols will be established in the case of concurrent events. The effects of such events on the study will be monitored, documented, and evaluated.

The intervention and control groups might experience prevention and control activities by health authorities whenever the school experiences a dengue outbreak. Considering that these activities are part of the standard care that both groups could receive during the study period, this condition will be controlled during analysis and interpretation. Information on these activities will be collected from both groups. The research outcomes based on this condition will be carefully interpreted.

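### The objectives call change inside one arm an effect of the module; only the between-group difference in change can be credited to iDEAL

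*Protocol article*

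**What the plan says.** The last paragraph of the Introduction lists the specific objectives. One is to "evaluate the within- and between-group effects of the iDEAL module in improving the KAP, environmental index, and dengue index" at T0, T1, T2 and T3. Within-group and between-group results thus stand side by side, both described as effects of the module.

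The Data analysis section gives the within-group part separate tests: "Within-group changes over time will be compared using one-way repeated measure analysis of variance (ANOVA) for continuous and normally distributed variables", with Cochran's Q for categorical data. The Methods part of the Abstract repeats both. The only decision rule is the general one, that p < 0.05 is significant. No sentence limits the within-group results to description.

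The same article also plans the controlled comparison. The Abstract and the Discussion state the hypothesis as improvement relative to the control group, and the Data analysis section plans a GLMM for main effects and interaction over the four time points.

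On other causes of change, the article says:
- Blinding: "The intervention and control groups will receive standard care, as it is part of the dengue prevention and control programme".
- Strengths and limitations: "The intervention and control groups might experience prevention and control activities by health authorities whenever the school experiences a dengue outbreak". It adds that "this condition will be controlled during analysis and interpretation".
- Introduction: "dengue is expected to peak in Malaysia in 2024". Study duration: "Data will be collected from 1st November 2023", in a study that ends in August 2025.
- Data collection: "The control group will undergo the same assessment as the intervention group at T_0_, T_1_, T_2_, and T_3". The Questionnaire section has the KAP questionnaire completed at each of these times.

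**The concern.** A change from T0 to a later visit inside the intervention arm is the sum of whatever the module did and whatever else happened. A test on that arm alone cannot separate the two, however well its standard error is computed. Inside the control arm, which receives standard care without iDEAL, the change cannot be a module effect at all, yet the objective's wording covers it.

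With that wording in place, a significant rise in the intervention arm could be reported as meeting an effectiveness objective even if the controls rose by the same amount. A pattern of significance in one arm and not in the other could likewise be presented as evidence without any test of the difference between arms. The article intends the results to inform public health policy and nationwide use of the module, so a pre-post gain labelled as an effect could mislead.

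**Working it through.** The plan states no figure on this point, so there is nothing to reproduce. The check has two parts.

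**1. What each contrast estimates.** Let δ be the mean change from T0 that would occur without the module, equal in expectation in the two randomised arms, and θ the module effect.
- Within the intervention arm: expected change = δ + θ.
- Within the control arm: expected change = δ.
- Between-arm difference in change: (δ + θ) − δ = θ.

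The within-arm tests have the null hypothesis of zero change, which is δ + θ = 0 in one arm and δ = 0 in the other. Neither is the hypothesis θ = 0. Only the group-by-time interaction addresses θ. If θ = 0, that test keeps its 5% level whatever δ is, provided clustering is modelled correctly.

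The question is then whether δ = 0 can be taken for granted. Four features of the article say that it cannot: the dengue programme continues in both arms; outbreak activities may reach either arm; a national peak is expected in 2024; and the same pupils complete the questionnaire four times, over roughly four months (delivery within one month of T0, follow-up to three months after it). The retest gain is an inference from the design; the article does not state one.

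**2. Illustration of size.** Inputs from the article: 800 pupils per arm (1600 / 2); 40 per class (1600 / 40 classrooms); significance level 0.05, taken as two-sided. Assumed, with no source in the article: drift d in SD units of the score; SD of change equal to the score SD (a correlation of 0.5 between visits); ICC of change of 0.02 to 0.05; full follow-up. The model is one paired T0-to-follow-up contrast in one arm with θ = 0.

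z = d × √(n / DE), with DE = 1 + (40 − 1) × ICC, and rejection probability ≈ Φ(z − 1.96).

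| Setting | DE | d = 0.10 SD | d = 0.20 SD |
|---|---|---|---|
| 800 independent pupils | 1 | z = 0.10 × √800 = 2.83; 81% | about 100% |
| ICC 0.02 | 1 + 39 × 0.02 = 1.78 | z = 2.12; 56% | 99% |
| ICC 0.05 | 1 + 39 × 0.05 = 2.95 | z = 1.65; 38% | 91% |

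The two clustered rows suppose that the test's standard error allows for the clustering.

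Sensitivity to follow-up: the Sample size estimation section cites a 70% attrition rate. If 30% remain (800 × 0.3 = 240 pupils, 12 per class) and the ICC is 0.05, DE = 1 + 11 × 0.05 = 1.55. A 0.10 SD drift then gives 24% (correlation 0.5) to 36% (correlation 0.7). A drift of 0.05 SD in the same setting gives 10% to 13%. Every scenario is above the nominal 5%.

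**The case against.** The strongest reply is that the right analysis is already in the plan. The hypothesis is a comparison with the control group, the GLMM interaction removes shifts common to both arms, and the Discussion ties the expected effectiveness result to the GLMM. The Data analysis section itself speaks neutrally of changes over time; the causal label sits in one phrase of the objectives. This stands, and it confines the point. A reader might infer that the plan would declare the module effective from a within-arm rise alone, or from significance in one arm only. The article states no such rule. The gap is that nothing excludes it: the objective names both results as module effects and does not say which decides.

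A second reply is that outbreak activities will be recorded in both groups and controlled for in analysis and interpretation. That partly covers this one cause. It does not cover a secular trend or retesting, and one-way repeated-measures ANOVA and Cochran's Q as named carry no covariate.

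A third is that the outside causes are possibilities. This stands too. The peak is expected and the outbreak activities might occur. A reader might infer that the epidemic peak falls between T0 and T3 and could make an effective module look harmful on the *Aedes* index. The text gives no calendar dates for T0 to T3, and the forecast rests on annual totals and a multi-year cycle, so that reading is not supported. The argument needs only that these causes cannot be excluded.

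Finally, the rejection probabilities rest on assumed inputs and describe one paired contrast, not the planned four-occasion ANOVA or Cochran's Q. That is correct; they illustrate the point and are not estimates for this trial. Within-group reporting is also customary and acceptable as description, and whether to print within-arm p-values is partly a matter of reporting preference.

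**Conclusion.** The point holds for the within-group part of the objective and its separate tests, and goes no further. As worded, uncontrolled pre-post change is labelled a module effect, including in an arm that does not receive the module. This follows from the design and needs no numerical assumption. Its practical size does: for an assumed 0.10 SD drift and no module effect, the false attribution rate in one paired contrast is about 81% with 800 independent pupils, 38% to 56% with an ICC of change of 0.05 to 0.02, and 24% to 36% if only 30% of pupils remain and the ICC is 0.05.

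It would be wrong to conclude that the trial's main comparison is compromised, or that background causes are known to move both arms. The between-group hypothesis and the GLMM interaction deal with common shifts, and nothing here changes the sample size. The wording should be corrected because it leaves open a second, uncontrolled route to a claim of effectiveness.

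**What to change.** 1. Introduction, specific objectives: state the objective as the between-group difference in change from T0 at T1, T2 and T3.
2. Data analysis, and Methods in the Abstract: name the group-by-time interaction from the GLMM as the sole basis for effectiveness conclusions.
3. In the same places, label within-group changes in both arms as descriptive, reported as estimates with confidence intervals, and say that no conclusion about effectiveness rests on them.

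This is a change of wording only. It needs no new data, visits or participants. The downside is fewer within-arm significance statements to report.

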## Methods

### Study design

This study is a two-arm, randomised, single-blinded, controlled parallel trial. Schoolchildren will be recruited and randomised to intervention and control groups based on selected clusters to avoid contamination. A cluster is defined as a comparable classroom based on a selected school that fulfils the inclusion and exclusion criteria. The intervention group will receive the iDEAL module, while the control group will receive standard education.

### Study duration

The study will be conducted over 24 months, from 1st September 2023 to 31st August 2025. Data will be collected from 1st November 2023. The study will comprise research planning, iDEAL module development, implementation, and evaluation of the intervention effectiveness. Fig 1 depicts the enrolment, intervention, and measurement schedule and corresponding assessment times.

**Fig 1 pone.0302736.g001:**
[figure not shown]
Enrolment, intervention, measurement, and assessment schedule.

### Study location

The study will be conducted in Selangor and Kuala Lumpur, which are dengue hotspots that recorded the most dengue cases in Malaysia [16]. Selangor (latitude 2° 35’–3° 60’ N, longitude 100° 45’–102° 00’ E) has a land area of 7,945 km^2^ and is one of the most developed and highly populated states in Peninsular Malaysia [17, 18]. Kuala Lumpur (3° 8’ 28.3” N, 101° 41’ 11.5” E) is located on the west coast of Peninsular Malaysia with a land area of 243 km^2^ [17]. In 2020, the Selangor population was 6,994,423 with a population density of 880/km^2^. Children comprised 29.5% of the Selangor population. The Kuala Lumpur population numbered 8,622,000 (population density: 8157/km^2^), which rendered it the most densely populated and urbanised location in Malaysia [17]. Kuala Lumpur is the Malaysian capital and a federal territory in Selangor, which significantly influences its social and economic development. Furthermore, the ecological flows, patterns, and processes of Selangor and Kuala Lumpur are interlinked. Therefore, the analysis will include Kuala Lumpur.

